### Activity

Accelerometers will be worn for 3 days before starting the cocoa and then for the third and sixth weeks (7 days each, 17 days in total) after starting. They will sample data at 25 Hz [18], and data will be averaged for each day. Participants will be reminded to initiate wearing the accelerometers by the lead researcher via text messages. The acceptance and adherence to wearing the accelerometers during this time will be assessed at the final assessment.

### Diet

A total of three 24-h dietary recalls will be administered to provide information about the diet of each participant and to determine any changes that may take place throughout the study. This method is less burdensome for patients than a 7-day food record diary yet will still provide an overall pattern in dietary behaviour throughout the study. Total energy intake is a potential confounder of the study and will therefore be corrected for in the analysis. We advise participants not to change their habitual diet and exercise regimes during the trial.

### Sample size

A sample size of 40 pwMS was deemed appropriate to address feasibility and determine variability of outcome measures [30–32] for a follow-on trial based on a 12-month recruitment period. Approximately five potentially eligible patients with recently diagnosed RRMS attend the clinic at the hospital per week, of which three will potentially fit the inclusion criteria of the study. Considering a recruitment rate of approximately 1.5 patients per week (50%), this would enable a minimum sample of 40 pwMS. The sample size of ≥ 30 also allows for assumptions from the central limit theorem in relation to representation within this group of RRMS with fatigue and should be easily recruitable within the timeframe.

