#### Recruitment

Recruitment will be evaluated based on the final number of participants who were successfully consented and randomised.

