### Trial status

The first participant was consented on the 15th of June 2016. The trial is currently recruiting until the 31st of August 2017.

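### Recruitment rate is a key objective, but recruitment is to be evaluated on the final number randomised, and a full count of 40 cannot show whether the assumed 1.5 per week and 50% uptake were met

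*Protocol article*

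**What the plan says.** **Objective.** The Objectives section of the protocol article names the recruitment rate, with reasons for non-recruitment, as one of the key results to come from the study.

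**Planning assumption.** The Sample size section states: "A sample size of 40 pwMS was deemed appropriate to address feasibility and determine variability of outcome measures". It assumes that recruiting will take 12 months. On patient flow it says: "Approximately five potentially eligible patients with recently diagnosed RRMS attend the clinic at the hospital per week". Three of these five are expected to be suitable. The section concludes: "Considering a recruitment rate of approximately 1.5 patients per week (50%), this would enable a minimum sample of 40 pwMS". It adds that a sample of at least 30 "also allows for assumptions from the central limit theorem in relation to representation within this group of RRMS with fatigue".

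**Evaluation.** The Recruitment subsection under Statistical methods says: "Recruitment will be evaluated based on the final number of participants who were successfully consented and randomised". It gives no time base, denominator or comparison value.

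**Fixed size.** The Methods part of the abstract and the Randomisation section set 40 participants, 20 in each arm.

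**Calendar.** The Consent section dates the start of recruitment to May 2016. Trial status gives the first consent as 15 June 2016 and says: "The trial is currently recruiting until the 31st of August 2017".

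**The concern.** A rate needs a numerator and a time or a denominator. The evaluation names only the numerator, and the design fixes that numerator in advance. If the trial reaches its target, the evaluated quantity is 40 whether recruitment took six months or fifteen, and whether half or a fifth of the suitable patients agreed.

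Recruitment rate and uptake are among the main things a feasibility trial hands to the planners of phase III. They set the number of sites, the length of the accrual period and the budget. If the assumed 1.5 per week and 50% are not checked, they may be carried forward untested.

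**Working it through.** **Inputs** (Sample size section unless stated): 3 suitable patients per week; 50% uptake; 1.5 recruited per week; 12 months, taken as 52 weeks; 40 in total, 20 per arm (Randomisation); first consent 15 June 2016 and close 31 August 2017 (Trial status).

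**Step 1. The plan's own rate.** 0.50 × 3 = 1.5 per week. This reproduces.

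**Step 2. What that rate yields in 12 months.** 1.5 × 52 = 78. Allowing only 48 or 50 working weeks gives 72 or 75. All exceed 40, so a minimum of 40 is consistent with the rate. The ratio is 78/40 = 1.95.

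**Step 3. What 40 requires.** At 1.5 per week, 40/1.5 = 26.7 weeks, about 6.2 months. To reach 40 in exactly 52 weeks, 40/52 = 0.77 per week, and 0.77/3 = 26% of the suitable patients.

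**Step 4. The calendar window.** 15 June 2016 to 31 August 2017 is 442 days, and 442/7 = 63.1 weeks. At 1.5 per week this window would give about 95. Forty spread over it would be 40/63.1 = 0.63 per week, which is 0.63/1.5 = 42% of the assumed rate.

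**Step 5. One final count, three different findings.** The eligible column assumes the stated flow of 3 per week. The interval is the exact Poisson 95% interval for 40 events over the weeks shown.

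| Final number | Weeks open | Randomised per week (95% CI) | Eligible at 3 per week | Share randomised |
|---|---|---|---|---|
| 40 | 26.7 | 1.50 (1.07 to 2.04) | 80 | 50% |
| 40 | 52 | 0.77 (0.55 to 1.05) | 156 | 26% |
| 40 | 63.1 | 0.63 (0.45 to 0.86) | 189 | 21% |

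The measure named in the Recruitment subsection is the first column and is the same in every row. The rate tells the rows apart: in the second and third, the interval excludes 1.5. So 40 participants are enough to test the planning rate once time is brought in.

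**Step 6. Whether another section supplies the rate.** Screening keeps a log of people approached, eligibility, and consent to be contacted. Eligibility reports the proportion eligible among those screened, which is a different ratio from randomised among eligible. The Feasibility subsection of the methods refers to eligibility, recruitment and retention in general terms. The Feasibility section of the discussion mentions the ability of centres to recruit and willingness to be randomised. None of them states randomised per unit time or randomised among eligible.

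**The case against.** The strongest reply is that recruitment is not judged on the count alone. Recruitment rate is a named objective, the screening log collects the material, and a final number combined with the dates in the article gives a rate by one division. A final number below 40 at the closing date would show a shortfall directly. The Recruitment subsection sets no pass mark, so nothing is declared a success by reaching 40. An exact interval is the kind of detail usually left to an analysis plan.

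Much of this stands. It limits the point to a trial that fills its target, and it shows that the data for the repair are already being gathered. It does not remove the mismatch: the article does name its recruitment measure, and that measure is not the one its objective calls for.

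A reader might infer more from the same sections, and the document does not support it:

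- *That the sample-size arithmetic is wrong.* The 40 is described as a minimum and as appropriate by reference to cited sources. It is not presented as rate times weeks, and 78 satisfies it.
- *That the n of at least 30 rule fails because arms have 20.* The article applies the rule to the whole group of patients, where 40 meets it. It makes no per-arm claim.
- *That the trial recruited at 42% of plan.* The article does not say how many were randomised by any date. The 63.1-week row is an illustration only.

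**Conclusion.** The point holds as a mismatch between the recruitment-rate objective and the stated recruitment measure. For a trial that fills, the count of 40 is compatible with 1.50, 0.77 or 0.63 per week, and with 50%, 26% or 21% uptake if 3 suitable patients appear each week. The conclusion rests on the fixed total of 40 and on 52 weeks to the year; 48 or 50 weeks leaves it unchanged. The assumed flow refers to a single clinic, whereas the Recruitment section of the methods lists four hospitals and self-referral. The true eligible pool may therefore be larger, which is a further reason to report uptake as well as pace.

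Two minor points go with it. The near-twofold gap between 78 and 40 is unexplained slack, and 40 as a minimum sits awkwardly beside a fixed 20 per arm. The central limit theorem concerns the sampling distribution of a mean; whether a sample is representative depends on how patients are selected. That sentence is not a valid rationale, though removing it changes no result.

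**What to change.** **Recruitment subsection (Statistical methods).** Replace the measure with two:

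1. Participants randomised per week open to recruitment, with an exact Poisson 95% confidence interval, compared with the 1.5 per week in the Sample size section.
2. The share of eligible patients who are randomised, taken from the screening log, compared with the assumed 50%.

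Keep the final number as a descriptive item and state the dates that define the open period.

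**Sample size section.** Say that 1.5 per week would give about 78 in 12 months, so that 40 needs only about 0.77 per week, or 26% of three. Keep 1.5 as the expected rate and present 0.77 as the rate needed. Reconcile the word *minimum* with the fixed 20 per arm. Delete the central limit theorem sentence.

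**Cost.** One additional summary from records already planned, some rewording, and possibly a less favourable recruitment figure. No extra participants, visits or measurements.

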### Data management

All work undertaken as part of this trial will comply with the Research Governance Framework for Health and Social Care UK and the OBU Research Governance Framework. All participant identification and referral procedures as well as procedures for data storage, processing and management will comply with the Data Protection Act 1998. All assessment data will be collected face-to-face using paper data collection forms. AE forms will be collected in person by one of the research team at OBU named in the delegation log. The retention period complies with guidelines set out by the OBU Research Governance Framework. Any individual who discontinues or deviates from the intervention will still have their data included in the data analysis.

### Safety monitoring

All chemicals required for assays will be purchased from Sigma-Aldrich, UK. SOPs have been approved by OBU and will be utilised for conducting all outcome assessments.

There are no expected serious adverse events (SAEs) in this study. The proposed procedures carry minimal risk to participants, and their care and comfort will be ensured throughout. This research will be performed in accordance with the International Conference on Harmonisation-Good Clinical Practice (ICH-GCP) standards. National Research Ethics Service ethical approval will be sought and confirmed before the start of the trial. The study will be overseen by a steering committee who will act as the data-monitoring committee to consider AEs and/or lack of adherence to the protocol (objection to having blood samples taken, lack of tolerance to the control/test drink).

### Randomisation

After recruitment, confirmation of eligibility, giving consent and collection of baseline data, patients will be registered and then randomised into one of the two groups, either the control or the test cocoa group. Participants recruited to the study will be randomly allocated the next available study number by the blinded assessor, with 20 participants in each group. The unblinded researcher will randomise participants into the control or intervention group using a computer-generated randomisation groups stratified for gender and DMTs.

### Blinding

This is a double-blind trial. One of the researchers on the trial will have access to the randomisation list, in which she will allocate participants randomly to either group. Each cocoa pack will contain a unique three-digit code, which will be determined by the unblinded researcher who will be able to trace the codes back to the cocoa group. All data collection will be conducted by a team of blinded assessors specifically trained in the methodology utilised for the collection of physical activity and functional assessments. Records of incidents where blinding is broken will be kept. All researchers who have contact with the participants will be blinded, including the main researcher on the trial. The main researcher and the statistician will remain blinded until after data analysis. Also, at the end of the intervention but before disclosure, participants will report their opinions of which group they believe they have been allocated to. A SAE could result in unblinding; however, this is unlikely as the principal investigator (PI) and the consultant medic on the trial will assess all AEs and SAEs and will make a decision of the action.

### Process evaluation

Upon exiting the study at assessment 3, each patient will be interviewed about queries regarding the intervention process, ease of adherence, tolerance and acceptability of the flavonoid drink and collection of outcome measures, and asked about any other issues or concerns arising from the trial. Participants will be asked their opinion on the importance of the research question proposed to inform future trials. We will also attempt to contact any participants who drop out of the intervention to ascertain reasons for discontinuing. Topics will include challenges to intervention delivery, perceived successes, barriers to implementation and suggestions on how to improve the intervention process. All participants who complete the trial only will be interviewed.

We will employ standard thematic analysis techniques. The transcripts of interviews will be closely examined to identify themes and categories. Codes will be applied to these broad themes, which will then be broken down further into sub-codes. Agreement on concepts and coding will be sought between members of the research team to ensure reliability. We will identify commonly expressed themes as well as unusual cases. A proportion of the data (20%) will be coded by two different team members to check on reliability of the coding scheme. The process of data collection and data analysis will be iterative, so that new themes emerge, and we will incorporate them into subsequent interview schedules. Process evaluation will include frequencies for adhering to the intervention, session content and progression which will be analysed descriptively with confidence intervals and regression where possible.

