### Outcomes

The primary aim of this study is to assess feasibility of the dietary intervention in terms of adherence, safety and process. This will be achieved through the documentation of adherence and any adverse events (AEs), as well as any health-related changes such as gastrointestinal disturbances that may occur during the intervention period. Duration of participation and dropout from the intervention will also be recorded. In order to assess benefits, a range of outcomes will be obtained. Outcome measures includeLevels of physical activity: wearable activity monitors (worn like a watch) [18] and the Physical Activity Scale for the Elderly (PASE) questionnaire [19]Dietary patterns assessed by a nutritionist: three 24-h dietary records [20]Fatigue levels: FSS, Neuro-QOL [21], and during the intervention, a Numerical Rating Scale (NRS) scored from 1 to 10, three times daily which classifies no fatigue as a 1 and very fatigued as a 10.Fatigability: performance on 6-min walk test (physical) [22] and the Adult Memory and Information Processing Battery (AMIBP; mental) [23]Blood markers of inflammation: TNF-alpha, reduced glutathione, a marker of antioxidant status and lipid peroxidationHealth descriptives: EQ5D5L [24] and the Preference-Based Multiple Sclerosis Index (PBMSI) [25], basic health questionnaire, Barthel ADL Index (BI) [26] and Hospital Anxiety and Depression Scale (HADS) [27]

Demographic factors and background factors will be assessed at baseline: medication, age, gender, level of education, type of MS, duration of disease, height, weight and leg length will be assessed at baseline. Participants will be stratified for gender and whether they are on first-line disease-modifying treatments or not.

Table 1 summarises the questionnaires that will be administered throughout the trial and at which visits these measures will be collected.

**Table 1 Tab1:** Outcome measures

Domain to be measured	Outcome measure(s)	Time required	When
Measures of overall health and questionnaires			
1. Health questionnaire and health assessment	General medicine use/health problems, etc.	10 min	1
2. Global fatigue	Neuro quality of life	5 min	1, 2, 3
3. Limitations in daily activity	Barthel Activities in Daily Living Index	5 min	1
4. Quality of life measure	EuroQOL 5D5L and Problem Based Multiple Sclerosis Index	5 min	1, 2, 3
5. Dietary recall	Monitor diet patterns	10 min	1, 2, 3
6. Consent	Verbal followed by written	10 min	1

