### Discontinuing

Participants will be advised to discontinue the trial if they find consuming the cocoa unacceptable or if consuming the cocoa is associated with in any related or unrelated AEs. Discontinuation of the trial will ultimately be decided by the PI and consultant medic.

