### Statistical methods

We will report summary statistics for demographics and outcome data of the study participants. The assessment of mediators is important to be able to identify the processes by which the intervention may bring about change. The proportion of adherence to the intervention will be reported descriptively with 95% confidence intervals. Graphical illustration will be used to check distributions of outcome data. As an exploratory trial, the primary outcome measures will be feasibility and acceptability. Results will be presented using point estimates, 95% confidence intervals and *p* values. The primary statistical analysis will be on an intention-to-treat basis, and the primary analysis will use the complete case data set. Exploratory analyses will be used to investigate the impact of individual demographic factors as well as theoretical mediators (i.e. disease/fatigue severity) on the intervention effect using appropriate correlation coefficients.

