#### Acceptability

The acceptability of the intervention will be measured through the end-of-study interview, which uses questions to measure the extent to which participants found the intervention and materials useful, enjoyable and beneficial.

Exploratory analyses will be used to investigate the impact of individual demographic factors as well as theoretical mediators on the short-term benefit of the intervention, using appropriate correlation coefficients.

A generalised linear model analysis will investigate whether fatigue differed between the treatment arms. This will be extended to joint modelling of both fatigue and physical functioning if there is a significant difference in the reported fatigue. Data may be transformed to improve model fit, or different regression approaches used (e.g. negative binomial or Poisson regression).

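### Acceptability, a primary outcome, is measured in an interview limited to completers, while people who find the drink unacceptable are advised to leave, so the interview result leans upward

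*Protocol article*

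**What the plan says.** Four statements in the protocol article bear on this point.

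- **Status.** Statistical methods: "As an exploratory trial, the primary outcome measures will be feasibility and acceptability".
- **Instrument.** Acceptability: "The acceptability of the intervention will be measured through the end-of-study interview". That section names no other instrument.
- **Timing and respondents.** Process evaluation: "Upon exiting the study at assessment 3, each patient will be interviewed about queries regarding the intervention process". The same paragraph ends: "All participants who complete the trial only will be interviewed".
- **Who leaves.** Discontinuing: "Participants will be advised to discontinue the trial if they find consuming the cocoa unacceptable". The advice concerns the trial, not just the drink. It extends to adverse events, and the final decision lies with the principal investigator and the consultant medic.

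Other parts of the article bear on what is known about those who leave. Process evaluation adds: "We will also attempt to contact any participants who drop out of the intervention to ascertain reasons for discontinuing". Outcomes adds: "Duration of participation and dropout from the intervention will also be recorded". Objectives lists reasons for loss to follow-up. Retention and Adherence, under Statistical methods, report loss to follow-up and discontinuation, and Adherence sets cut-offs at 75% and 65%. The Feasibility section of the Discussion encourages sites to keep assessing people who stop the intervention, where this is possible.

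**The concern.** A primary outcome should be measured in everyone randomised, or at least in a group whose membership does not depend on the answer. Here a stated rule ties the two together: finding the drink unacceptable is a reason to leave, and leaving means not being interviewed. The interview then describes acceptability among people who tolerated the drink well enough to finish.

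This is not a detail that could sit in an unseen analysis plan, because the article states the restriction outright. Acceptability is also the first listed objective and one of the considerations meant to shape the phase III trial. If adherence falls between 65% and 75%, the team will consider adjusting the intervention. Those who left because of the drink are best placed to say what to adjust, and they would not have been asked the acceptability questions.

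**Working it through.** **Reading the sections together.** Acceptability is a primary outcome (Statistical methods). It is measured by the end-of-study interview (Acceptability). That interview takes place at assessment 3 and covers completers only (Process evaluation). Those who find the cocoa unacceptable are advised to leave the trial (Discontinuing). No sentence says that drop-outs receive the acceptability questions, or how their reasons for stopping enter the acceptability result.

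**Is there a figure to reproduce?** No. The article gives no acceptability rate, acceptability threshold or expected drop-out rate. It does not define a percentage finding the drink acceptable either: interviews are analysed thematically, and the Acceptability section speaks of the extent to which participants found the intervention useful, enjoyable and beneficial. The arithmetic below only shows direction and sensitivity.

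**Inputs.**
- N = 40 randomised (Abstract, Methods).
- A = true proportion finding the drink acceptable (assumed).
- s = share of dissatisfied participants who leave before assessment 3 (assumed).
- Participants who accept the drink are assumed to stay.

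**Formula.** Apparent acceptability among completers = A·N / (N − s·(1 − A)·N).

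**Worked case.** With A = 60%, 24 accept and 16 do not. With s = 50%, 0.5 × 16 = 8 leave, and 40 − 8 = 32 are interviewed. The result is 24/32 = 75%, which is 15 points above 60%.

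| Assumed A | s = 0 | s = 25% | s = 50% | s = 75% | s = 100% |
|---|---|---|---|---|---|
| 50% (20/40) | 50% | 20/35 = 57% | 20/30 = 67% | 20/25 = 80% | 20/20 = 100% |
| 60% (24/40) | 60% | 24/36 = 67% | 24/32 = 75% | 24/28 = 86% | 24/24 = 100% |
| 80% (32/40) | 80% | 32/38 = 84% | 32/36 = 89% | 32/34 = 94% | 32/32 = 100% |

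The completers' figure exceeds the truth whenever s > 0, and stops depending on the truth only at s = 100%. If some who accept the drink also leave, the bias shrinks, and it vanishes when both groups leave at the same rate. The advice in Discontinuing makes higher leaving among the dissatisfied the expected pattern.

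**Would the adherence criterion reveal it?** Only partly. If completing the trial is read as adherence, 30 of 40 meets the 75% criterion. Suppose all 10 who left rejected the drink and 90% of the 30 completers accepted it. The interview would show 27/30 = 90%, against 27/40 = 67.5% of those randomised, with adherence still classed as successful. In the extreme case of A = 60% and s = 100%, completion would be 24/40 = 60%, below the 65% cut-off and plainly visible.

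**The case against.** The strongest reply is that people who reject the drink are not invisible. Dropout is recorded, every drop-out is to be contacted for reasons, loss to follow-up and discontinuation are reported, and adherence has its own cut-offs. The steering committee also considers lack of tolerance to the drinks (Safety monitoring). Leaving is not automatic, and someone who stops the drink but still attends assessment 3 could be interviewed. All of this stands, and it rules out several stronger readings:

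- **That acceptability will look good whatever the truth.** Completers can still report poor acceptability, and the table shows the result losing touch with the truth only if every dissatisfied participant leaves.
- **That nothing is learned from those who leave.** Their reasons for stopping are sought.
- **That the trial cannot inform the phase III decision.** The only stated rule for adjusting the intervention or piloting further rests on adherence, and acceptability is one input among several.
- **That Process evaluation flatly contradicts itself.** A brief contact about reasons for drop-outs and a full interview for completers can coexist, although the wording is loose.

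The reply does not remove the core point. A contact about reasons is not the acceptability interview, and separate dropout figures leave the result of the named primary outcome uncorrected.

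**Conclusion.** The point holds in this limited form. The stated measure of a primary outcome is confined to completers, while a stated rule steers those who find the drink unacceptable out of the trial. Interview-based acceptability is therefore biased upward to the extent that dissatisfied participants leave more often than others.

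The size is unknown. The 15-point gap in the worked case rests wholly on assumed values (true acceptability of 60%, half of the dissatisfied leaving, no one else leaving) and on treating acceptability as a yes/no proportion, which the article does not define. Across the assumed values in the table the gap runs from 0 to 50 points (100% against 50%). It should not be quoted as an expected error. On its own, the completers' result is not a sound summary of acceptability among those randomised; read beside dropout, reasons and adherence it is still informative.

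**What to change.** 1. In Process evaluation, replace the completers-only sentence so that the same acceptability questions are offered to everyone randomised: at assessment 3, or at the already planned contact for those who stop.
2. Reconcile Process evaluation, Discontinuing, Acceptability and the Feasibility section of the Discussion, so that it is clear who has left the drink, who has left the trial, and who is still assessed and interviewed. This concerns consistency and data collection only; which clinical rule on stopping applies is for the trial team.
3. Report acceptability by arm for all randomised participants. Show beside it how many stopped because of the drink and how many were not reached, and give the completers-only result as secondary.
4. If those who stopped because of the drink are counted as not accepting it, present that as a supporting summary, since it merges acceptability with discontinuation, which is already assessed separately.

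The cost is a change of wording and a few short extra calls to people the team already intends to contact. Some who stop will not answer, so the bias will be reduced rather than removed. The change is best made while recruitment continues, because views not collected when people leave are hard to recover later.
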